## 7.0 TREATMENT PLAN

### 7.1 Sorafenib Dose Levels and Definition of Dose-Limiting Toxicity

Evaluation for loco-regional toxicity from therapy will occur daily (excluding weekends and holidays) while patient is receiving RT (**see section 10.1 for study calendar**) and then biweekly during the rest period following completion of RT prior to surgical resection. Evaluation for generalized/systemic toxicity (e.g. hypertension, myelosuppression, etc.) will occur weekly (**see section 10.1 for study calendar**) during the treatment phase and then biweekly during the rest phase of the study. Patients will maintain a pill diary so that a record of self-administered medications will be available.

| Dose Level | Sorafenib          | Radiation       |
|-------------------|---------------------------|------------------------|
| 1                 | 200 mg twice daily        | 200 cGy x 25 fractions |
| 2                 | 200 mg q am
400mg q pm | 200cGy x 25 fractions  |
| 2                 | 400 mg twice daily        | 200 cGy x 25 fractions |

A traditional dose-escalation design will be used to determine the MTD of sorafenib combined with radiotherapy. The MTD is defined as the dose that produces dose limiting toxicity (DLT) in 33% of patients. Three patients will be enrolled per dose level, with escalation to the next dose level if no dose-limiting toxicity (DLT) is observed. If one DLT is observed, the dose level will be expanded to a total of 6 patients, and escalation will occur if no more than one DLT is observed among the 6 patients. If 2 or more out of 3 patients, or 3

or more out of 6 patients experience DLT, the study will be terminated or dose reduced to the previous dose level. Dose level escalation will be determined based on DLTs observed from start of treatment until date of surgery, but DLTs will be monitored in the postoperative period, and dose de-escalation may occur if excess late DLTs are observed.

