DLT is defined as: grade 4 anemia, grade 4 neutropenia lasting > 7 days, grade 3-4 thrombocytopenia with clinically significant bleeding or grade 4 thrombocytopenia lasting > 5 days, and grade 3-4 non hematologic toxicity (except: nausea/vomiting that responds to anti-emetic therapy; grade 3 neutropenic fever lasting  $\leq 5$  days; grade 3 encephalopathy lasting  $\leq 2$  days; grade 3-4 hypokalemia, hypophosphatemia, hypomagnesemia, hypocalcemia unless requiring hospitalization; grade 3 diarrhea controlled with medication within 2 days; and grade 3 grade hypertension that is adequately controlled with medication (BP <150/100)).

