## 13.0 STATISTICAL CONSIDERATIONS

### 13.1 Primary Objective

#### 13.1.1 Phase I Trial

To determine the maximally tolerated dose (MTD) of the antiangiogenic agent sorafenib in combination with preoperative conformal radiotherapy for soft tissue sarcomas of the extremities and the body wall, high grade > 5 cm in diameter and low grade > 8 cm. A traditional dose-escalation design will be used to determine the MTD of sorafenib combined with radiotherapy. 3-6 patients will be evaluated at each of 2 dose levels, based on a starting dose of 200 mg bid derived from preclinical studies of sorafenib combined with radiotherapy. Since 400 mg bid is the well established MTD for sorafenib monotherapy in patients with renal cell carcinoma and hepatocellular carcinoma, the dose will not be escalated above this level even if DLT is not observed.

MTD is defined as the dose that produces dose limiting toxicity (DLT) in 33% of patients. Dose level escalation will be determined based on DLTs observed through the first 70 days of therapy, but DLTs will be monitored in the post-operative period. Dose de-

escalation may occur if excess late DLTs are observed. **See Section 7.1 for further explanation of determination of DLT.** Briefly, if 0/3 patients experience DLT, the dose will be escalated for the next cohort of 3 patients. If 1/3 patient experience DLT, the same dose will be repeated for the next cohort of 3 patients. If 2/3 or 3/3 patients experience DLT, the study will be terminated or dose reduced. Toxicity and wound complication rates will be reported.

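### The Phase I DLT definition stops at grade 4, so a treatment-related death with no earlier listed event would not count against escalation or against the dose taken into Phase II

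*Protocol*

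**What the plan says.** Section 7.1 defines DLT by a closed list. The hematologic items are anemia and prolonged neutropenia at grade 4, and thrombocytopenia at grade 3-4 with significant bleeding or at grade 4 if prolonged. The non-hematologic item is "and grade 3-4 non hematologic toxicity (except: nausea/vomiting that responds to anti-emetic therapy", followed by further exceptions. Section 13.1.1 adds no definition of its own: "See Section 7.1 for further explanation of determination of DLT".

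The decision rule in 7.1 is "Three patients will be enrolled per dose level, with escalation to the next dose level if no dose-limiting toxicity (DLT) is observed". Then: "If one DLT is observed, the dose level will be expanded to a total of 6 patients", with escalation allowed if at most one of the six has a DLT. Section 13.1.1 agrees: "if 0/3 patients experience DLT, the dose will be escalated for the next cohort of 3 patients".

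On timing, 7.1 says "Dose level escalation will be determined based on DLTs observed from start of treatment until date of surgery". For the period after surgery it says that "dose de-escalation may occur if excess late DLTs are observed".

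Three other places bear on the reading:

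- The Phase II Treatment Stop Rule, also in 7.1, counts adverse events of grade 3 and anything above.
- Section 7.2.3 describes grade 4 hypertension as life-threatening, which puts a fatal outcome beyond grade 4.
- Section 4.0 lists three sorafenib doses and caps escalation at 400 mg twice daily. Section 3.1 carries the Phase I MTD into Phase II.

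**The concern.** The most serious toxicity is the one that the definition does not name. The list has no open-ended grade, so a patient who dies of treatment without first having a listed event contributes nothing to the DLT count. The rule then acts on that count and can send the next cohort to a higher dose. The provision for late toxicity also counts DLTs, so it has the same gap.

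Such a death is possible on the protocol's own account. Section 8.1 lists myocardial ischemia or infarction, hypertensive crisis and hemorrhage as uncommon drug-related events. It also mentions cerebral hemorrhage, arrhythmia and thromboembolism, with causality not established. The Synopsis says that safety data for sorafenib with radiotherapy are limited.

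**Working it through.** The plan gives no figure for this point, so there is none to reproduce. The check applies the 7.1 rule to the literal definition and then to a definition that counts the death.

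**Decisions.** The deaths here have no earlier listed event, and any listed DLT is in another patient.

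| Outcome at a dose level | As written | Death counted |
|---|---|---|
| 3 patients: 1 death, no listed DLT | 0/3, escalate | 1/3, expand to 6 |
| 3 patients: 1 death, 1 listed DLT | 1/3, expand to 6 | 2/3, terminate or reduce |
| 3 patients: 2 deaths, no listed DLT | 0/3, escalate | 2/3, terminate or reduce |
| 6 patients: 1 death, 1 listed DLT | 1/6, escalate | 2/6, no escalation |

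These consequences for escalation apply at 200 mg twice daily and at 200 mg/400 mg. At 400 mg twice daily there is no higher dose, and the effect is that the death would not count against accepting that dose for Phase II.

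**Conditional chance of escalating.** Suppose exactly one such death among the first three patients and none later. Let p be the rate of listed DLTs in the other patients and q = 1 − p. The documents give no p for the lower doses. Values of 10%, 20% and 33% are assumed, the last being the DLT rate by which the protocol defines the MTD.

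- As written, escalation follows if the other two patients have no listed DLT (q²). It also follows if exactly one of them does and the next three have none (2pq × q³). P = q² + 2pq⁴.
- With the death counted, the other two and the next three must all be free of DLT. P = q² × q³ = q⁵.

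| p | As written | Death counted |
|---|---|---|
| 0.10 | 0.810 + 0.131 = 0.941 | 0.9⁵ = 0.590 |
| 0.20 | 0.640 + 0.164 = 0.804 | 0.8⁵ = 0.328 |
| 0.33 | 0.449 + 0.133 = 0.582 | 0.67⁵ = 0.135 |

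For the single case of one death and no listed DLT in the other two, escalation is certain as written. With the death counted it needs three further patients without a DLT: q³ = 0.73, 0.51 or 0.30.

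**The case against.** The strongest reply is that this is drafting shorthand. A fatal hemorrhage, arrhythmia or embolism is usually life-threatening first, and so is already a grade 4 DLT. For the gap to matter, a toxic death must have no graded precursor, the rest of the cohort must not trigger the rule, and the investigator must score the death as no DLT, which is unlikely. Section 6.2 excludes recent cardiac, thrombotic and bleeding events. Section 1.6 reports no toxic deaths in the cited sorafenib monotherapy trials. Section 12.5 sends fatal unanticipated problems to the IRB within 7 days, and 12.3 allows an urgent change for an immediate hazard.

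All of this lowers the likelihood, and it stands to that extent. It does not repair the rule:

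- The monotherapy record does not settle the safety of the combination.
- Sections 7.7, 12.3, 12.5 and 12.6 deal with stopping an individual's treatment, urgent changes and reporting. None alters the DLT count.
- The close monitoring is mainly local: "Evaluation for loco-regional toxicity from therapy will occur daily (excluding weekends and holidays) while patient is receiving RT". Systemic toxicity is evaluated weekly during treatment and biweekly in the rest phase, so a sudden death between evaluations could leave no graded precursor.

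A reader might also infer that the Phase II stop rule has the same hole, because it counts events in ten patients who have all been resected. The documents do not support that. The rule is already open-ended in grade, and the accrual pause reviews all safety data to date, which would include a death before surgery. Counting events in every patient who had started treatment, against an unchanged threshold of four, would make stopping materially stricter. At an assumed 35% event rate (the wound-complication figure in section 1.2, used only as an illustration), the chance of four or more is about 49% with 10 patients and 65% with 12.

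**Conclusion.** The gap is real but narrow. Followed as written, the Phase I rule escalates from either of the two lower doses after a cohort with one treatment-related death, no earlier listed event in that patient and no other DLT. At the top dose it ignores the death when the Phase II dose is accepted. No other section corrects this.

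A reader might infer that the protocol disregards toxic deaths in general, or that 94% against 59% describes how the design performs. Neither follows. Most fatal toxicities would first register as a listed event, and an investigator would probably count the death in any case. The percentages are conditional on such a death having occurred, on no further one, and on assumed DLT rates. The documents give no rate for the death itself, so its overall effect cannot be sized. The change is still worth making: the consequence is serious, the correction is small, and a prespecified escalation rule should not rely on someone overriding its text after a death.

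**What to change.** In section 7.1:

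- Change the non-hematologic limit from grade 3-4 to grade 3 or greater.
- State that the listed exceptions apply to non-fatal events only.
- State that any death between start of treatment and surgery that is at least possibly related to sorafenib/RT is a DLT.
- State that later deaths at least possibly related to sorafenib/RT are late DLTs under the existing de-escalation provision.

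Section 13.1.1 needs no separate wording because it refers back to 7.1. The Phase II stop rule stays as it is.

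The cost is one changed phrase and two or three sentences in an amendment, with no new visit, committee or data item. The downside is that a dose level may occasionally expand to six, or not escalate, after a death.

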#### Treatment Stop Rule

Furthermore, a pause in study accrual will be implemented in the phase II portion of the trial after 10 patients have completed concurrent sorafenib plus conformal radiotherapy followed by surgical resection. Safety assessment will be made 6 weeks following resection of the 10th patient (9 – 13 weeks following completion of concurrent sorafenib and RT) to ensure that excess DLTs are not observed. The study will be ***terminated for safety*** (not lack of efficacy) if 4 of these 10 patients experience grade 3 adverse events or greater since this would represent an increase from the baseline rate of serious AEs expected from the standard combination therapy of preoperative radiation and surgical resection. This pause in accrual will allow us to review all safety data collected to date. If DLTs in excess of our stopping rule are not observed, then the phase II trial will continue to the targeted accrual of 25 patients.

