### 1.2 Surgery with External Beam Radiotherapy

For patients with localized STS amenable to resection with curative intent, surgical treatment in combination with RT results in local disease control in 76% to 92% of patients with successful limb preservation, i.e. avoidance of amputation, in 90 to 95% of patients whose tumors are located on the extremity. Although function-sparing surgery combined with RT represents a significant advance for patients with STS, this approach still requires total en bloc excision of the primary tumor with a goal of 2 centimeters of normal tissue around the tumor in all directions. These operations risk significant morbidity for the patient.

An important component of local therapy in STS is adjuvant RT. Adjuvant RT for patients with STS of the extremity has been shown to reduce local recurrence rates by 20 to 25% relative to radical resection alone. The timing of RT administration (preoperative versus postoperative) has been compared in a randomized clinical trial. This trial demonstrated that preoperative RT was associated with a statistically significant increase in perioperative wound complications (35% vs. 17%). Conversely, at a median follow-up of 6.9 years, preoperative RT was associated with a statistically significant decrease in long term complications, such as joint fibrosis, joint stiffness, and extremity edema (23% vs. 36%). Although these data have been interpreted in different ways by different investigators, advocates of preoperative radiotherapy maintain that the data favor the preoperative administration of RT since perioperative wound complications are generally reversible whereas late complications of radiotherapy are generally irreversible. Furthermore, although considered a secondary endpoint of the trial, overall survival was statistically improved in the patients who received preoperative radiotherapy (85% vs. 75% at 3 years,  $P=0.048$ ). Although these secondary survival data regarding neoadjuvant RT should be viewed with caution, it is reasonable to hypothesize that neoadjuvant RT in combination with novel systemic agents may improve both local and distant disease-control in patients with STS.

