## 7.2 Sorafenib Dose Modification

7.2.1 General Considerations. According to the following dose level table, sorafenib dosing will be modified for adverse events that are at least in-part *attributable* to sorafenib according to the following sections.

| Dose Level | Sorafenib            |
|------------|----------------------|
| 0*         | 200 mg daily         |
| 1          | 200 mg twice daily   |
| 2          | 200mg am
400mg pm |
| 3          | 400 mg twice daily   |

\*Patients will be removed from protocol treatment if dose reduction below this level is indicated.

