Resectability will depend upon the judgment of the operating surgeon. For the extremities, resection must be limb salvage procedure. Extremity patients who are not resectable without amputation may be amputated. Unresectable tumors may be palliated with surgery, chemotherapy, or additional radiation therapy. These patients will be taken off protocol.

**Note that documentation of wound complications is an integral part of this clinical trial. Wound complications are defined in section 10.4.2 and must be accurately recorded and reported.**

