#### 7.7 Duration of Therapy

Treatment should continue until the end of protocol therapy or until one of the following criteria applies:

- Disease progression,
- Intercurrent illness that prevents further administration of treatment,
- Unacceptable adverse event(s),
- Greater than 3-week delay in therapy due to adverse event,

- Patient presents with a positive beta-HCG test,
- Patient decides to withdraw from the study,
- General or specific changes in the patient's condition render the patient unacceptable for further treatment in the judgment of the investigator.

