#### Treatment Stop Rule

A pause in study accrual will be implemented in the phase II portion of the trial after 10 patients have completed concurrent sorafenib plus conformal radiotherapy followed by surgical resection. Safety assessment will be made 6 weeks following resection of the 10th patient (9 – 13 weeks following completion of concurrent sorafenib and RT) to ensure that excess DLTs are not observed. The study will be **terminated for safety** (not lack of efficacy) if 4 of these 10 patients experience grade 3 adverse events or greater since this would represent an increase from the baseline rate of serious AEs expected from the standard combination therapy of preoperative radiation and surgical resection. This pause in accrual will allow us to review all safety data collected to date. If DLTs in excess of our stopping rule are not observed, then the phase II trial will continue to the targeted accrual of 25 patients.

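### The 4-of-10 phase II safety boundary counts only patients who complete sorafenib/RT and are resected, so toxicity that prevents completion can escape the rule

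*Protocol*

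**What the plan says.** The Treatment Stop Rule appears in the same terms in Protocol Sections 7.1 and 13.1.2. Accrual pauses "after 10 patients have completed concurrent sorafenib plus conformal radiotherapy followed by surgical resection". The timing is tied to surgery: "Safety assessment will be made 6 weeks following resection of the 10th patient". The study ends for safety "if 4 of these 10 patients experience grade 3 adverse events or greater". The pause is also meant to allow a review of all safety data gathered so far, but no threshold attaches to that review, and continuation to 25 patients is made conditional on the stopping rule.

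Other sections describe how a patient can leave before completing:

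- Section 7.7 ends treatment for unacceptable adverse events and for "Greater than 3-week delay in therapy due to adverse event".
- Section 7.2.1, at the lowest sorafenib level: "Patients will be removed from protocol treatment if dose reduction below this level is indicated".
- Section 7.2.3 takes patients off protocol therapy for grade 4 hypertension, or when a hold for hypertension exceeds 21 days.
- Section 7.5, on unresectable tumors: "These patients will be taken off protocol".

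No section says that a patient who leaves by one of these routes counts toward the 4, enters the 10, or prompts an earlier look.

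**The concern.** The group to which the boundary applies is selected on an outcome that toxicity can itself change. If patients with grade 3 or greater events are more likely than others to miss completion or surgery, the event rate among completers is lower than the rate among all patients treated, and the boundary is reached less often than it should be. In the extreme case, a toxic death before surgery adds nothing to the count.

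Phase I does not work this way. Section 7.1 counts DLTs from the start of treatment among the patients enrolled at each dose level, with no requirement that they complete. The phase II rule departs from this without giving a reason. It guards a combination for which the Synopsis says safety data are limited, in patients treated with curative intent.

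**Working it through.** The protocol gives a boundary but no error rate or power for it, so there is no stated figure to reproduce.

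**Inputs from the protocol.** Denominator 10 and boundary 4, read as 4 or more (Sections 7.1 and 13.1.2).

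**Assumptions.** The true share p of treated patients with a grade 3 or greater event, taken as 35%, 40%, 50% and 60%. The share q of those patients who do not complete, taken from 0 to 50%. Patients without an event are assumed to complete. The protocol gives neither p nor q. The 35% is borrowed from the wound-complication rate with preoperative RT in Section 1.2, which is not a grade 3 or greater adverse event rate.

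**Step 1. Rate among completers.** pc = p(1 − q) / (1 − pq). This is below p for any q above 0. For p = 50%:

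- q = 10%: 0.45/0.95 = 47.4%
- q = 20%: 0.40/0.90 = 44.4%
- q = 30%: 0.35/0.85 = 41.2%
- q = 50%: 0.25/0.75 = 33.3%

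**Step 2. Chance of stopping.** P(X ≥ 4), with X binomial(10, pc). At q = 0 and p = 50% this is 1 − (1 + 10 + 45 + 120)/1024 = 848/1024 = 82.8%. The full grid is:

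| True rate p | q = 0 | q = 10% | q = 20% | q = 30% | q = 50% |
|---|---|---|---|---|---|
| 35% | 48.6% | 42.2% | 35.3% | 28.2% | 14.3% |
| 40% | 61.8% | 55.3% | 48.0% | 39.9% | 22.4% |
| 50% | 82.8% | 78.2% | 72.2% | 64.7% | 44.1% |
| 60% | 94.5% | 92.4% | 89.3% | 84.7% | 68.7% |

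The q = 0 column is also the result of counting the first 10 treated patients. A simulation at p = 50%, q = 30% gave 64.6%, against 64.7% from the formula.

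**Step 3. Exposure before the look.** The expected number treated to obtain 10 completers is 10/(1 − pq). At p = 50% and q = 30% this is 10/0.85 = 11.8 patients, of whom 11.8 × 0.5 = 5.9 have an event. If all treated patients counted, the figures would be 10 and 5.0.

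**The case against.** The strongest reply is that few patients would be lost and that the denominator has a purpose.

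- **Most grade 3 events do not end treatment.** Sections 7.2.2 to 7.2.4 largely provide for holding and resuming, and for several events at grade 3 for no action. Section 7.7 says when treatment stops; it does not say that radiotherapy or surgery is cancelled when sorafenib is. A postoperative wound event cannot remove a patient from the count at all. These points argue for a modest q. The only discontinuation figure in the protocol is fewer than 10% for toxicity on sorafenib monotherapy (Section 1.6). As a rough guide, 10% of all treated patients lost, all with events, at p = 50% is q = 20%, a fall from 82.8% to 72.2%.
- **The rule needs operated patients.** Its comparator is preoperative radiation plus resection, and wound events arise only after surgery. That justifies waiting for the postoperative period. It does not justify dropping patients whose toxicity kept them from surgery.
- **All safety data will be reviewed at the pause.** Patients who left are therefore not invisible. A discretionary stop remains possible, but it is not the written rule.

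A reader might infer that the patients with the worst toxicity are all outside the 10. The protocol does not establish this. Completion of concurrent sorafenib is undefined, so someone who drops sorafenib but finishes radiotherapy and is resected may count; only patients who never reach resection are excluded on every reading. Unresectability is also not in itself a toxicity category. A reader might also fix on one large figure, such as the 21-point drop (82.8% to 61.8%) if a third of patients with events do not complete at p = 50%. Neither input is in the protocol. Finally, one might object that patients who start before the pause go uncounted. Some overrun comes with any postoperative look, the protocol gives no accrual rate to size it, and changing the denominator would not remove it.

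**Conclusion.** The point holds. As written, the only numeric phase II safety boundary leaves out patients whose toxicity prevents resection, and possibly those who stop sorafenib early for toxicity. The direction is certain for losses of this kind: each removes an event from the count, and the rule then leans toward continuing. The size is not known. At an assumed true rate of 50%, the loss in the chance of stopping is 4.6 percentage points at q = 10% (82.8 − 78.2), 10.6 at 20%, 18.1 at 30% and 38.7 at 50%. These figures assume that everyone without an event completes. Whether 4 of 10 is well calibrated to the baseline the rule invokes is a separate question, which this point leaves open.

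**What to change.** Amend the Treatment Stop Rule in Sections 7.1 and 13.1.2, keeping the 4-of-10 threshold:

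1. Define the 10 as the first 10 phase II patients who receive any sorafenib or radiotherapy, and count any grade 3 or greater event whether or not the patient completes treatment or surgery.
2. Hold the look once each of the 10 has either reached 6 weeks after resection or, if never resected, has left protocol treatment and had adverse events assessed. Timing from the 10th resection alone would fail if one of the 10 is never operated on.
3. Report separately any of the 10 who left before surgery for reasons other than toxicity and without an event. They cannot have a wound event, so they dilute the rate in the opposite direction.

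The cost is a few sentences and no extra patients. Adverse events are already graded at each visit (Section 10.4.1). Section 10.4.3 limits follow-up after protocol therapy to recurrence, metastasis, survival and late toxicity, so the assessment of a patient who leaves early should be stated explicitly. The downside is that the rule triggers more readily, also when the true rate is not excessive: at 35% the chance of stopping is 48.6%, rather than 42.2% with q = 10% or 28.2% with q = 30%. The sponsor should accept that knowingly.

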#### 7.4 Radiation

Initiation of conformal radiotherapy will be considered day 1 of study treatment. Treatment will consist of a total dose of 50 Gy (delivered in 25 fractions of 200 cGy over approximately 35 days). If treatment falls on a weekend or holiday, treatment can resume the next business day. The target volume of radiation therapy will include the site of the primary lesion and those tissues suspected of involvement by microscopic disease to a clinically important probability. Physical exam in conjunction with MRI and/or CT scans obtained during evaluation will be used to define the target volume. Treatment planning will aim to include a radial margin of approximately 2 cm and a longitudinal margin of approximately 3 cm beyond the gross disease.

Optimal field arrangement, beam parameters, and shaped blocks will be used to achieve the closest approximation of treatment volume to target volume to minimize irradiation of uninvolved normal tissue. Immobilization devices will be used daily to ensure reproducibility of treatment protocols. All possible efforts will be made to avoid treating the full circumference of an extremity or treating the lung. Patients may receive post-operative brachytherapy or external beam radiation therapy for positive microscopic surgical margins. Boost will not be given for patients with 100% necrosis. If indicated, RT may begin approximately 2 weeks following surgical resection, assuming there is satisfactory healing of the surgical wound. The target volume for the post-operative RT will be the tumor bed as defined by the operative and pathological findings.

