#### 7.5 Surgery

Surgical resection will take place on approximately day 50 – 90 of the study, occurring approximately 3 to 7 weeks following completion of combined neoadjuvant sorafenib/RT (**see study calendar, section 10.1**).

Surgical treatment necessary to resect the tumor with negative margins will be used. Biopsy sites will be excised en bloc with the definitive surgical specimen. The goal of surgical resection is to remove a 2 cm margin of normal tissue around the tumor without compromising function. Surgical dissection will take place through normal tissue planes and, where technically possible, will be done through a fascial plane outside the tumor. If the tumor is close to or displaces major vessels or nerves, these structures will be preserved if the adjacent adventitia or perineurium can be removed and the margin is not involved pathologically. If postoperative pathologic evaluation reveals positive soft-tissue margins other than bone, nerve, or large blood vessels, this margin should be re-resected if possible. If bone, major blood vessel, or nerve is microscopically positive, additional radiation may be given as noted above. In general, lymph node dissection will not be performed, but a sampling can be performed if the primary tumor is over a major node station. Closed wound suction drainage should be used in all anatomic regions to evacuate postoperative seroma fluid. The drains should exit the skin close to the edge of the surgical incision. External

compression for extremity resections with ace wraps or compression dressings is also advised. Because all patients will have had radiation, special care must be given to skin flaps. Use of muscle flaps, pedicled myocutaneous flaps, and even free flaps is encouraged to fill dead space, particularly if there is any concern about the viability of the wound flaps. In general, the following principles should be followed in post-operative management of these patients:

- Maintain staples or skin sutures per surgeon preference but because of potential delay in wound healing, 3-4 weeks is recommended
- Leave drains until the drainage meets the criteria for surgeon preference for discontinuation
- Begin rehabilitation slowly

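### The Phase II safety count (4 of the first 10 patients) is read once, 6 weeks after the 10th resection, and no sentence suspends accrual if the 4th affected patient is known sooner

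*Protocol*

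**What the plan says.** Sections 7.1 and 13.1.2 carry the same Treatment Stop Rule. It has four parts.

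- **Pause.** In Section 7.1, "a pause in study accrual will be implemented in the phase II portion of the trial after 10 patients have completed" sorafenib with radiotherapy and then resection.
- **Look.** "Safety assessment will be made 6 weeks following resection of the 10th patient", which the protocol places 9 to 13 weeks after the end of sorafenib/RT.
- **Boundary.** The study is terminated for safety "if 4 of these 10 patients experience grade 3 adverse events or greater".
- **Otherwise.** If the rule is not exceeded, "then the phase II trial will continue to the targeted accrual of 25 patients".

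Neither section says what happens to accrual if a 4th affected patient is known before the 10th resection. Neither gives a count for patients 11 to 25.

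**The concern.** The boundary is a count in a closed set of 10 patients. Once four of them qualify, no later outcome can bring the count back under the limit. Waiting for the 10th resection and 6 more weeks therefore adds nothing to the stopping decision, while new patients can keep starting. The pause also comes late for its own purpose. It is triggered by the 10th resection, weeks after that patient starts, so patients 11 onward can start in the meantime. At stake are patients who begin a combination that the trial's own rule has already settled should stop.

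**Working it through.** **1. The protocol's own figure.** Section 7.5 places surgery "occurring approximately 3 to 7 weeks following completion of combined neoadjuvant sorafenib/RT". Adding 6 weeks gives 3 + 6 = 9 and 7 + 6 = 13 weeks, which matches the stated 9 to 13. Section 7.4 has radiotherapy "delivered in 25 fractions of 200 cGy over approximately 35 days", about 5 weeks. So the 10th resection, and with it the pause, comes 5 + 3 = 8 to 5 + 7 = 12 weeks after patient 10 starts. The look comes 14 to 18 weeks after that start.

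**2. Inputs that the protocol does not give.** The true rate p of grade 3 or greater events on the combination is unknown, so I use 35% to 60%. The 35% in Section 1.2 is for wound complications after preoperative RT, not for all grade 3 or greater events, so it only marks the neighbourhood. The accrual rate is not given either; I assume 1 to 2 patients per month. Patients are taken as independent.

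**3. Probability of reaching the boundary, and when.**

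- P(X ≥ 4) = Σ C(10,x) pˣ(1−p)¹⁰⁻ˣ, summed over x = 4 to 10.
- P(4th affected patient is the k-th enrolled) = C(k−1,3) p⁴(1−p)ᵏ⁻⁴.
- P(among the first nine, given that the boundary is reached) = 1 − P(k = 10)/P(X ≥ 4).

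At 40%, P(k = 10) = 84 × 0.4⁴ × 0.6⁶ = 0.100, so 1 − 0.100/0.618 = 0.84.

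| True rate | P(boundary reached) | 4th affected is among first nine | Mean position of 4th | 10 minus mean |
|---|---|---|---|---|
| 35% | 0.486 | 0.80 | 7.8 | 2.2 |
| 40% | 0.618 | 0.84 | 7.6 | 2.4 |
| 50% | 0.828 | 0.90 | 7.0 | 3.0 |
| 60% | 0.945 | 0.95 | 6.35 | 3.65 |

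**4. An earlier trigger does not change these probabilities.** Four or more affected among 10 is the same event as the 4th affected patient being one of the 10. Summing the second formula over k = 4 to 10 returns the second column of the table. Acting on the 4th patient changes when the rule acts, not how often.

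**5. How many patients would be spared.** The last column of the table assumes that each patient's outcome is known before the next one starts, so it is an upper bound. In practice enrolment overlaps and some events are postoperative. Simulating random (Poisson) arrivals at a 60% rate gives the mean number of the first 10 who start after the 4th event is known:

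| Assumed timing of events | 1 per month | 2 per month |
|---|---|---|
| During RT only | 3.1 | 2.6 |
| Spread over days 0–126 | 1.9 | 0.8 |
| Spread over days 56–126 | 1.3 | 0.3 |

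Day 126 is 18 weeks, the latest time of the look from step 1. Counting everyone who starts between knowledge of the 4th event and the 10th resection, the same assumptions give about 2.4 to 7 patients. The larger figure arises because patients 11 onward are not held back: 8 to 12 weeks at 1 to 2 per month (4.345 weeks per month) is 8/4.345 × 1 = 1.8 to 12/4.345 × 2 = 5.5 further starts after patient 10.

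**6. After the look.** Patients 11 to 25 are 15 of 25, or 60% of Phase II. A true rate of 40% passes the look with probability 1 − 0.618 = 0.382, and a rate of 50% with probability 1 − 0.828 = 0.172.

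**The case against.** **The rule may already bind at once.** The termination sentence is conditional on the count and does not say that a met condition must wait for the assessment. An investigator or the IRB could also stop the trial at any time. A reader might therefore go further than the text in either direction. To say that the protocol requires accrual to go on after a 4th event is too strong, because it is silent. To say that it stops accrual is not supported either, because both the pause and the assessment are tied to the 10th resection. The silence is what needs correcting.

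**Other safeguards exist.** Toxicity is evaluated daily or weekly on treatment (7.1), dose-modification rules apply to each patient (7.2), and events go to the IRB and FDA (12.5, 12.6). Late DLTs are monitored with possible de-escalation, in the Phase I text. These limit the harm, but none is a numeric trial-level boundary for Phase II.

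**The saving may be small.** This stands in part. A reader might take 3 to 4 of the first 10 patients as the expected saving; that is the ceiling. With late events and fast accrual, fewer than one of the first 10 would be spared.

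**A later boundary.** A reader might infer that patients 11 to 25 need a further look, and that 11 or more of 20 would serve because it is reached 5% of the time at a 35% rate and 76% at 60%. Those figures are unconditional. A trial gets to 20 only after passing with at most 3 of 10, so it would need at least 8 of the next 10. The look then adds 0.13 to 0.8 percentage points of stopping at rates of 35% to 60%. A boundary with real effect has a price. Carrying the 40% proportion forward (4, 6, 8 and 10 affected at 10, 15, 20 and 25 patients) raises stopping from 0.828 to 0.948 at a 50% rate, but also from 0.486 to 0.616 at 35% and from 0.350 to 0.441 at 30%. The protocol does not show that omitting it is an error.

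**Conclusion.** The concern holds as a gap in timing. The rule has a fixed count but no written action when that count is reached early, and under the assumed rates it would usually be settled before the 10th patient's outcome is needed (0.80 to 0.95 of the times it is reached). The benefit of closing the gap is about 0.3 to 3 of the first 10 patients, or about 2 to 7 counting all starts before the 10th resection. Those ranges rest on a 60% true rate, 1 to 2 patients per month and the event timings shown above, none of which the protocol gives. The gap is worth correcting because doing so leaves the probability of reaching the boundary unchanged at every true rate. The lack of a numeric boundary for patients 11 to 25 is a fact to note; whether to add one is the sponsor's trade-off between detection and false stops.

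**What to change.** In Sections 7.1 and 13.1.2, add that accrual is suspended, and the existing 4-of-10 rule applied, as soon as a 4th of the first 10 Phase II patients is known to have a qualifying event. Keep the assessment 6 weeks after the 10th resection for the case where 4 has not been reached. Use one definition of a qualifying event throughout: the paragraph sets the boundary on grade 3 or greater adverse events but makes continuation depend on DLTs, whose definition in Section 7.1 has exceptions, and the two must be reconciled.

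The cost is a running count of events already collected, and possibly an earlier suspension, for instance while a grade is being confirmed. The 4-of-10 threshold is not altered. If the sponsor chooses to add a boundary for patients 11 to 25, its stopping probabilities should be calculated conditional on having passed the first look and reported with it.
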